| Exposures, Outcomes and CovariatesExposure: breast cancer Women will be considered exposed at the day of the breast cancer diagnosis (index date), denoted by the first entry of one or more of the Read codes provided in appendix 2. Primary outcomes: anxiety and depression To our knowledge, there is no validated list of Read codes to identify anxiety and depression in the CPRD GOLD primary care database. Algorithms will be developed and tested to identify anxiety and depression cases in CPRD. The algorithms will be chiefly determined by clinical diagnoses of anxiety and depression registered in the EHR with Read codes, and supplemented with information from drug prescriptions, referrals, and symptoms (if deemed suitable). Please see section N, plan of analysis for specific aim 1, for more details on the construction and validation of algorithms. Secondary outcomes: fatigue, mild cognitive impairment, pain, sleep disturbance, sexual dysfunction, and fatal and non-fatal self-harm Similarly, we will develop and test outcome-specific algorithms that identify events using a hierarchy of data on clinical diagnoses, prescriptions, referrals and symptoms.  In sensitivity analysis, we will consider linked data (see section J for data linkage requested) to develop more precise definitions of the outcomes, when possible. For example, two definitions of suicide will be considered: (1) considering Read codes only to identify suicides in CPRD; (2) considering Read codes for suicide as well as death registration data where suicide was recorded as primary cause of death (ICD-10 codes provided in appendix 3) Covariates Variables considered as potential confounders or effect modifiers of the association between breast cancer history and anxiety and depression (the primary outcomes of this study) are described below. The directed, acyclic graph (DAG) in appendix 4 explicitly describes the assumptions of the causal relations between the variables that underpin the choice. Please refer to the data analysis (section N) for details on which variables will be considered for sensitivity analyses only. *Potential confounders*  - Age at diagnosis (categorical variable, in 10-year age bands)   Defined as the absolute difference between the year of breast cancer diagnosis and year of birth. Age is a strong risk factor for breast cancer and for mental disorders.   - Alcohol drinking habits at diagnosis (categorical variable: current drinker, former drinker, never drinker)   Excess alcohol drinking is a well-established risk factor for breast cancer [30], besides being positively associated with anxiety and depression [31-33]. The most recent data on alcohol drinking habits prior to index date will be used in analysis. Current drinking will be further sub-divided into high, moderate, low or unknown intake of alcohol.   - Body mass index at diagnosis (categorical variable: underweight, normal weight, overweight, obesity class I, obesity class II and above)   Calculated as BMI=(weight/height^2^). Higher body mass index is protective against breast cancer in pre-menopausal women, but a risk factor for breast cancer post-menopause [34]. Obesity increases the risk of anxiety and depression [35, 36]. The most recent recording of BMI prior to index date will be used in analysis. The BMI values will be categorised into 5 categories: <18.5 kg/m^2^ (underweight), 18.5-24.9 kg/m^2^ (normal weight), 25.0-29.9 kg/m^2^ (overweight), 30.0-34.9 kg/m^2^ (obesity class I), ≥35.0 kg/m^2^ (obesity class II and above). Read codes for body weight categories recorded in the year prior to the breast cancer diagnosed will be considered to supplement missing information for this variable.   - Calendar period of diagnosis (categorical variable: ≤1994; 1995-1999; 2000-2004; 2005-2009; 2010-2014; >2014)   Even though calendar time *per se* does not change the risk of breast cancer, the risk of being diagnosed with breast cancer changed over time, probably due to increase awareness of the disease along with widespread use of mammography to screen for breast cancer. Time has also contributed for mental disorders being more likely to be diagnosed, due to raises awareness and increased recognition of the importance of mental disorders among health care professionals.   - Diabetes mellitus (dichotomous variable: yes/no)   Diabetes mellitus has been associated with an increased risk of breast cancer [37] and depression [38]. Algorithms previously defined elsewhere will be applied to identify patients with diabetes mellitus in the CPRD GOLD primary care database [39, 40].   - Level of deprivation (categorical variable: quintiles of patient-level IMD).   The IMD is an ecological measure of deprivation for small areas in England that combines information from seven domains (income, employment, education, health deprivation, crime, barriers to housing, and living environment), and ranks the small area from 1 (most deprived) to 32,844 (least deprived). Patients will be categorised in quintiles of IMD, with quintile 1 representing those least deprived and quintile 5 those most deprived.   - Menopausal status (dichotomous variable: premenopausal/postmenopausal)   Menopausal status is a potential confounder of the association between breast cancer history and depression, as the risk of breast cancer increases with menopause [30], and so does the risk of depression [42]. However, information on menopausal status is not easily available in the CPRD database. We will therefore produce results stratified by an age cut-off, as a proxy of the menopausal status of the women. The cut-off will be the mean/median age at natural menopause in the UK.   - Smoking history at diagnosis (categorical variable: current smoker, former smoker, never smoker)   Information on Read codes available on the data will be used to classify patients by smoking history. The most recent data on smoking prior to index date will be used in analysis. *Potential effect modifiers*  - Living alone (dichotomous variable: yes/no)   Ascertained from the CPRD GOLD primary care data using Read codes (list provided in [41]) and the patient’s family number (variable ‘famnum’ from the patient file). Women living in household of <2 people will be classified as living alone.   - Residing in a care home (dichotomous variable: yes/no).   This variable will be defined from the CPRD GOLD primary care database, using Read codes (list provided in [41]), and information gathered in the family number variable (‘famnum’). For the latter, ‘care home’ will be defined as a household with >3 individuals aged ≥65 years and if their total count was more than of individuals <65 years.   - Ethnicity (categorical variable: White, South Asian, Black, Others and mixed)   Ethnicity data recorded in the CPRD GOLD primary care database will be categorised in five groups, following the categories defined in the UK 2011 Census: White, South Asian, Black, Others and mixed. This variable will be derived from Read codes available in the CPRD GOLD primary care database and from HES, since the combined data sources increase completeness from 55% to 79% [41]. For analysis, four groups will be considered: White, South Asian, Black, Others and mixed.   - Previous mental health history (categorical variable: yes/no)   Mental health history will be defined as having had an episode of anxiety- or depression-related disorders (primary outcomes) or any the secondary outcomes, ever recorded at more than 1 year before the breast cancer diagnosis (patients who had the outcome in the year before the breast cancer diagnosis will be excluded from the cohort). These will be identified based on the algorithms defined in aim 1 of this study.   - History of stroke or coronary heart disease at diagnosis (two dichotomous variables: yes/no)   These will include ischaemic heart disease (angina and myocardial infarction) and stroke, which are amongst the leading causes of disability-adjusted life years in females in the UK. These will be identified through Read codes recorded in the CPRD GOLD primary care database.   - Socioeconomic status (IMD quintiles of deprivation)   The IMD is an ecological measure of deprivation for small areas in England (Lower Super Output Areas). It combines information from seven domain indices (income, employment, education, health deprivation, crime, barriers to housing, and living environment). The index ranks the areas from 1 to 32,844; usually the quintiles are used for research purposes: from 1 (most deprived) up to 5 (least deprived). The IMD is linked to the primary care data using the postcode of the patient or practice. *Potential mediators of the association between breast cancer history and anxiety/depression*  - Sequelae from cancer treatments (six separate binary variables (yes/no): lymphoedema, pain, mild cognitive impairment, fatigue, sexual dysfunction, sleep disorder)   Lymphoedema will be defined using Read codes for the condition, in the CPRD GOLD primary care database. Pain, mild cognitive impairment, fatigue, sexual dysfunction, and sleep disorder are secondary outcomes of this study, and will be identified based on the algorithms defined in aim 1 of this study. Patients will be classified as having had one of these conditions if there was more than one record for these conditions within a 6-month interval.   - Exposed to endocrine treatment for breast cancer: binary variable (yes/no).   This will be defined from the CPRD GOLD primary care database using Read codes for at least two prescriptions of anastrozole, tamoxifen, exemestane, or letrozole [43] within a 6-month period. |

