| Data/ Statistical AnalysisPrimary analysesSpecific aim 1. To develop and validate algorithms to identify patients with anxiety and depression Algorithm development  A systematic review is currently under way to identify the lists of Read codes previously used to define anxiety and depression of primary care databases in the UK. The systematic review search expressions are provided in appendix 5.  *(A) Raw data tabulations*  We will estimate the number and proportion of patients recorded during the observation period with:   1. Diagnostic Read code for anxiety/depression; 2. Prescription of anxiolytics/antidepressants; 3. Referred to mental health services; 4. Symptoms of anxiety/depression.   Proportions will be estimated by calendar year.  *(B) Simpler algorithm*  We will estimate the additional contribution of prescriptions, referrals and symptoms to identify cases of anxiety/depression in CPRD. Referrals and prescriptions of anxiolytics/antidepressants will be considered as sufficient to identify cases of anxiety/depression if a Read code for symptoms of anxiety/depression, respectively, were recorded during the previous year. The reasons for this are threefold: (1) there is good evidence that GPs switched from anxiety/depression diagnostic codes to symptomatic ones [44, 45], following claims of over diagnosis of these conditions; (2) antidepressants and anxiolytics have also other indications, including anxiety disorders for antidepressants [46], which raise questions of the use of these data their own to identify these outcomes; (3) pharmacological treatment of mild depression has been discouraged since 2004 [47], and thus referrals to psychotherapy may help to capture milder cases.  *(C) Complex algorithm*  A more detailed algorithm will be developed considering that some drugs are prescribed for both depression and anxiety, in addition to manage vasomotor symptoms, which may be more frequent in breast cancer survivors than in women who did not have cancer. An example for depression is given in appendix 6. We will estimate the number of patients with anxiety/depression at each step, to evaluate how much each category adds to what has been previously recorded.  Algorithm validation  A random sample of 1 million patients of both sexes will be selected from the CPRD GOLD primary care database. We will apply each algorithm and produce descriptive statistics stratified by likelihood of having the outcome, including:   - Number and proportion of patients with the anxiety, depression or both, by 3-year calendar period; - Number and proportion of patients with the anxiety, depression or both, by 3-year calendar period, age and sex; - Number and proportion of patients with the anxiety and depression by 3-year calendar period and country in the UK.   For each outcome, we will compare the estimates obtained with others obtained from the literature, prioritising national surveys of population-based data such as the following:   - Adult Psychiatric Morbidity Survey 2007 [48] and 2014 [49]; - Measuring National Well-being programme, made available by the Office for National Statistics (includes prevalence of those in the UK with some evidence indicating depression or anxiety, since 2013, by country in the UK and English regions, and by 10-year age groups up to 75 years) [50].   The final algorithm will be chosen by considering information in the numeric value closer to the estimates obtained from the literature. Sensitivity analysis Proportion estimates considering the presence of symptomatic codes within the previous year will be re-calculated to consider shorter periods of time (i.e. 3 and 6 months). Specific aim 2. Risk of mental health outcomes in women who had breast cancer compared to women who did not have cancer**Primary outcomes analysis – depression and anxiety**Main analysis Descriptive statistics including number of events observed and person-years at risk will be computed, overall and stratified by the covariates listed in section M (see above). Medical procedures for the diagnosis of breast cancer are likely to cause anxiety. To deal with this we planned to exclude patients who had a record of anxiety diagnosed within 1 year before the breast cancer; this could result in patients with higher levels of trait anxiety being excluded from the analysis. We will calculate the number and proportion of patients who were excluded because they had the outcome in the year prior to the breast cancer, stratified by month. We will also describe how many of those who were excluded from analysis had an outcome after the breast cancer diagnosis by age-group. The quintiles of the distribution of the number of consultations (defined using the ‘consid’ variable) will be described, as this can indicate the patterns of seeking care between women with a history of cancer, compared to those who did not.  The association between breast cancer history and anxiety and breast cancer history and depression, will be quantified using Cox regression models with time since index as the underlying time scale, and stratifying on matched set to account for matching by age and primary care practice. Follow up will begin at the index date (vide section M for definition of the exposure) and will terminate when an outcome is observed. Women will be censored at the earliest date of any of these: cancer recurrence, other cancer diagnosis, death, transference out of the practice; if these events don’t occur, censoring will be observed at the date of last data collection for the practice. Crude measures of the association between breast cancer history and anxiety and depression will be reported stratifying by the covariates described in section M.  Cox multivariate regression analysis will be use to estimate hazard ratios adjusted for calendar period of breast cancer diagnosis, menopausal status, and diabetes mellitus at baseline (see list of confounders in section L, covariates, for the definition of these variables).  Interaction terms between the exposure and the following variables will be added, to explore effect modification by ethnicity (White, South Asian, Black, Others and mixed), place of residence (care home vs. household), co-habitation status (living alone vs. cohabiting), SES (quintiles of IMD), having mental health disorders history (yes vs. no), having history of stroke (yes vs. no) and coronary heart disease (yes vs. no).  Confidence intervals will be calculated using robust estimates of the standard errors, to account for the fact that patients may also contribute with time at risk in the unexposed cohort prior to their cancer diagnosis.  The proportional hazards assumption will be tested in two ways: 1) graphically, by plotting the cumulative rates on a log scale; 2) inferentially, by applying a likelihood ratio test to the estimates obtained for the entire period of observation and for time split into intervals. Sensitivity analyses Sensitivity analyses planned for this study will include a subset of patients only; this is because they use variables from linked data, which is available for a fraction of the patients only, and include variables amenable to have missing data (i.e. BMI, alcohol intake, smoking and patient-level IMD). Regarding the latter, we will quantify the completeness of each variable to decide on their inclusion in the final models. Analyses including variables with missing data will be restricted to patients with complete data for covariates (complete case analysis), if missing data is likely to be missing not a random. The following sensitivity analyses are planned:   1. The main analysis will be repeated further adjusting for age at diagnosis (continuous variable, since matching allowed for 3-year gap), patient quintile level of IMD, alcohol drinking patterns prior to index date, smoking history and body mass index categories prior to index date. 2. We will exclude women diagnosed with the outcome of interest in the year prior to the cancer diagnosis. To account for the fact that treatment for these conditions may often last for more than one year, and that mild anxiety and depression may be treated in psychological services and not result in visits to the GP, we will repeated the main analysis including only patients who had 5 years of complete follow up prior to the index date and did not have the outcome recorded at any point during this period.  Multiple comparisons We acknowledge that this study includes multiple comparisons for each outcome, and several outcomes. Thus, P-values in the range ~0.01-0.05 be considered as some statistical evidence of an effect and interpreted cautiously. Sample size considerations considering a 0.01 probability of type I error (α) are provided in see section I. Specific aim 3. To estimate association between breast cancer history and anxiety/depression by presence of lymphoedema, pain, mild cognitive impairment, fatigue, sexual dysfunction, sleep disorders, and having done endocrine therapy, during the follow up period. We will estimate the cumulative incidence and period prevalence of lymphoedema, pain, mild cognitive impairment, fatigue, sexual dysfunction, and sleep disorders, in breast cancer survivors during the overall follow up period and by 5-year of follow up period.  We will estimate the hazards of developing anxiety and depression (the main outcomes) for three groups of patients: 1) breast cancer survivors who did not develop the common complication (i.e. lymphoedema, pain, mild cognitive impairment, fatigue, sexual dysfunction, sleep disorders) up to time *t*; 2) breast cancer survivors who have had the common complication at time *t*; 3) women who never had cancer. A Cox regression model will be used to estimate the association between time-updated exposure and the main outcomes (anxiety and depression), having as reference the hazard observed for the women who did not have cancer. The exposure variable will be time-updated; this means that women who develop a common complication will contribute with information to group 1 until the date at which they develop the complication of interest; after this point they will contribute with information to group 2. All models will be adjusted for calendar period of breast cancer diagnosis.  Confidence intervals will be calculated using robust estimates of the standard errors. Sensitivity analyses planned in objective 2 will be applied to this objective as well. Secondary outcomes analyses – fatigue, mild cognitive impairment, pain, sleep disturbance, sexual dysfunction, fatal and non-fatal self-harm The steps outlined above will be repeated for the secondary outcomes. Sensitivity analysis will follow the same rationale as described for the primary analysis. |

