| Plan for addressing confounding The confounding effect of age and socio-economic status (SES) will be limited at the study design phase, as  women who had breast cancer will be individually matched to women who never had cancer by age and primary  care practice. Variables considered as important confounders will be included in the multivariate Cox regression  models (vide section M, covariates). |
| Plans for addressing missing data There are no plans for using multiple imputation methods in this study. Three variables in the main analysis are likely to have missing data: body mass index, smoking and alcohol intake. The probability of these values being recorded in the patients’ medical records is likely to depend on the actual value (e.g. obese patients may have their weight more often assessed and smoking may be more often recorded in patients who visit the GP for complications of smoking (e.g. chronic obstructive pulmonary disease). This is a direct violation of the missing at random assumption needed for multiple imputation. We will therefore conduct a complete case analysis, which is a valid method when missingness is conditionally independent of the outcome [52]. |
| Patient or user group involvement (if applicable) No patients were involved in the drafting of this protocol. |
| Plans for disseminating and communicating study results, including the presence or absence of any restrictions on the extent and timing of publication The results of this study will be presented at scientific conferences in the area, and submitted for publication in peer-reviewed journals.  **Conflict of interest statement:** [name] reports that CPRD has financial relationships with its clients, including the London School of Hygiene and Tropical Medicine, in relation to providing access to research data and services outside the submitted work. [name] reports personal fees from Roche, Clinigen, Eli Lilly, and Novartis, not related to this work. [name] reports grants from Wellcome Trust, the Royal Society, Medical Research Council, and British Heart Foundation, outside the submitted work. |

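### The main aim 3 Cox model names only calendar period and does not say that matched-set stratification is kept, so its complication-specific hazard ratios may be confounded by age and practice

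*Protocol*

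**What the plan says.** All references are to the Protocol.

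- **Data/Statistical Analysis, Specific aim 2, main analysis.** The Cox model uses time since index, "stratifying on matched set to account for matching by age and primary care practice". The hazard ratios are "adjusted for calendar period of breast cancer diagnosis, menopausal status, and diabetes mellitus at baseline".
- **Data/Statistical Analysis, Specific aim 3.** This aim gets its own model description: "A Cox regression model will be used to estimate the association between time-updated exposure and the main outcomes (anxiety and depression"). There are three groups: survivors without the complication so far, survivors with it, and women without cancer as reference. On the split, "women who develop a common complication will contribute with information to group 1 until the date at which they develop the complication of interest"; after that date they count in group 2. Then: "All models will be adjusted for calendar period of breast cancer diagnosis". Standard errors are robust. One item is expressly brought over from aim 2: "Sensitivity analyses planned in objective 2 will be applied to this objective as well".
- **Exposures, Outcomes and Covariates, potential confounders.** "Age is a strong risk factor for breast cancer and for mental disorders".
- **Plan for addressing confounding.** "The confounding effect of age and socio-economic status (SES) will be limited at the study design phase", that is, by individual matching on age and practice. A general sentence adds that important confounders enter the Cox models.
- **Study Design.** Comparators share the index date of their matched case. Practice is controlled by matching because it has too many levels to model.

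**The concern.** Matching balances all survivors against all comparators at the index date. It does not balance the survivors who later develop a complication against the pooled comparators. Once survivors are divided by a post-index condition, the age and practice mix of group 2 can differ from that of the reference group. Control then has to come from the analysis, either by stratifying on matched set or by modelling age and practice. The aim 3 text names neither.

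At stake are the main aim 3 hazard ratios for anxiety and depression by lymphoedema, pain, mild cognitive impairment, fatigue, sexual dysfunction, sleep disorder and endocrine therapy. The lowest effects cited for diagnosed anxiety and depression in the sample size table are 1.06. A distortion of several per cent in either direction is therefore the size of an effect the study hopes to see.

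**Working it through.** The protocol gives no power, error rate or expected hazard ratio for aim 3, so there is no figure to reproduce.

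**1. The two specifications side by side**

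| Element | Aim 2 main model | Aim 3 main model |
| --- | --- | --- |
| Stratified on matched set | stated | not stated |
| Calendar period | stated | stated |
| Menopausal status, diabetes | stated | not stated |
| Robust standard errors | stated | stated |
| Sensitivity analyses | defined | carried over expressly |

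Calendar period is constant within a matched set because the index date is shared. In a stratified model, the only adjustment aim 3 names would do nothing.

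**2. Expected hazard ratio without stratification, no true effect**

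Let w be the share of women in an age band, h the relative outcome hazard and c the relative complication rate. To a first approximation, ignoring depletion over follow-up:

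null HR (group 2 vs cancer-free) ≈ [Σwch / Σwc] ÷ Σwh

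Inputs: the feasibility Table 1 age bands. The 45–54 count is taken as 13,235, which fits the printed 25.3% and the total of 52,335; the printed 12,235 does not. Band midpoints are used. The gradients are assumptions. Example: outcome HR 0.8 and complication rate ratio 1.3 per 10 years of age, with age 60 as reference.

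| Age | w | h | Share of group 2, wc/Σwc |
| --- | --- | --- | --- |
| 18–24 | 0.0005 | 2.361 | 0.0002 |
| 25–34 | 0.0147 | 1.953 | 0.0065 |
| 35–44 | 0.0939 | 1.562 | 0.0538 |
| 45–54 | 0.2529 | 1.250 | 0.1882 |
| 55–64 | 0.2849 | 1.000 | 0.2756 |
| 65–74 | 0.2448 | 0.800 | 0.3078 |
| 75–80 | 0.1083 | 0.669 | 0.1680 |

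Mean hazard is 0.967 in group 2 and 1.046 in the comparators, so the null HR is 0.967/1.046 = 0.92. The same formula gives 1.17 for 0.8/0.6, 0.83 for 0.8/2.0 and 0.99 for 0.9/1.1. It gives exactly 1.00 if either gradient is absent. If the outcome rises with age (1.25/1.3), it gives 1.08, so the direction reverses.

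For practice, with log-normal effects of SD 0.4 on outcome and on complication recording and correlation 0.5, the null HR ≈ exp(0.5 × 0.4 × 0.4) = 1.08.

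**3. Simulation under the null**

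Each run had 52,335 sets matched 1:4, with a time-updated three-group exposure and no effect of cancer or complication.

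*Setting A* (assumed: 2 events per 100 person-years at age 60, follow-up uniform over 0–12 years, complication in about 6% or 20% of survivors; 300 replicates):

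| Outcome / complication gradient per 10 years | Unstratified HR | Rejection at 5% |
| --- | --- | --- |
| 0.8 / 0.6 | 1.16–1.18 | 82% to >99% |
| 0.8 / 0.8 | 1.07 | 20–46% |
| 0.8 / 1.3 | 0.92–0.93 | 24–59% |
| 0.8 / 2.0 | 0.83–0.84 | 85–100% |
| Practice link only (as in step 2) | 1.07–1.08 | 22–51% |

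Stratified on matched set: HR 0.99–1.01, rejection 4–7%.

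*Setting B* (assumed: 1.5 events per 100 person-years at age 60, censoring uniform over 0–12 years capped at 10, complication in 10–30% at 5 years, calendar period controlled; 250 replicates):

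| Gradient per 10 years | Unstratified HR | Rejection at 5% |
| --- | --- | --- |
| No age or practice link | 1.00 | 4% |
| 0.9 / 1.1 | 0.985 | 7% |
| 0.85 / 1.2 | 0.97 | 14% |
| 0.8 / 1.3 | 0.94 | 50% |
| 0.8 / 0.7 | 1.10 | 82% |
| 0.7 / 1.5 | 0.85 | 99.6% |
| Shared practice effect, log-SD 0.3 | 1.04–1.07 | 22–60% |

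Stratified on matched set: HR 0.99–1.00. Rejection was 4–6% in nine of ten scenarios and 9.6% in one, where the HR was 1.002.

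**4. Price of stratifying**

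Under the null, with k comparators per survivor still at risk, the variance of the group 2 log HR is about (1/d)(1 + 1/k), where d is the number of group 2 events. Against a very large pooled reference it is about 1/d. The standard error ratio is √(1 + 1/k): 1.12 for k = 4, 1.15 for k = 3, 1.22 for k = 2 and 1.41 for k = 1.

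**The case against.** The strongest reply is that the aim 3 text is silent on stratification and does not drop it. Aim 3 also leaves the time scale, start of follow-up and censoring unstated, and these plainly carry over. The imported sensitivity analysis justifies adding continuous age by the gap that matching allows, which makes most sense if the matching is kept in the analysis. Aim 2 also lists calendar period although it is stratified, so naming it in aim 3 does not prove an unstratified model. The confounding section promises important confounders in the Cox models generally.

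This stands in part: a reader might infer that aim 3 is specified as unstratified, and the protocol does not say so. It does not remove the point. Aim 3 describes its own model, repeats two aim 2 features, and imports only the sensitivity analyses by name. An analyst following the paragraph literally would fit the unstratified model.

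A reader might also infer that the aim 3 results would reject because of age and practice rather than cancer with complications. The protocol does not support that. It gives no complication frequency by age or practice, and bias needs both links. The false rejection rates also owe much to the large sample. Nor does the protocol say that aim 3 exists to rank complications; it aims to estimate associations.

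The sensitivity analysis does add age. It does so together with deprivation, alcohol, smoking and body mass index, in a subset with linked or complete data, and it adds no practice term.

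**Conclusion.** The point holds as a gap in the stated adjustment of a named aim on the primary outcomes, and it should be closed before analysis. As written, the main aim 3 model does not secure the age and practice control on which the design relies, and no planned analysis recovers practice.

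The consequence is conditional. Across the assumed gradients the null hazard ratio ran from about 0.83 to 1.18; with mild gradients it was 0.97–0.985, and with no link 1.00. The sign depends on whether the outcome rises or falls with age, which the protocol does not quantify. Shifts of this size could mask or mimic effects near the lowest cited value of 1.06. They could not alone produce the larger cited depression ratios of 1.39 to 1.94. The aim 2 comparison is not affected.

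**What to change.** In specific aim 3, replace the sentence on calendar period with a statement that the Cox models for the three-level time-updated exposure are stratified on matched set and adjusted for menopausal status and diabetes. These are the aim 2 covariates that can vary within a set. Calendar period cannot, and adds nothing there.

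If an unstratified model is preferred for precision, put age at index (flexibly) and a practice-level term in the main aim 3 model, not only in the sensitivity analysis.

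The cost is one sentence, no new data, and a model option already used in aim 2. Intervals widen because each survivor is compared only with her own remaining comparators: about 12% on the standard error with all four at risk, and more as sets deplete.
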